#### RAISE User Engagement and Acceptability

RAISE app use metrics will be generated through logs from the Chorus platform. The use metrics will be examined in relation to the outcomes of interest (eg, changes in parenting stress) through bivariate correlations and linear regression and included as control variables when examining intervention effectiveness. Average response rates to daily ratings will be examined, as well as factors that relate to response rates (age, gender, race, mental health, substance use, etc) through bivariate correlations (eg, age) and independent samples *t* tests (eg, gender).

Descriptive statistics will be used to examine ratings of application usability (eg, ease of platform use) and acceptability of intervention components (content, mindfulness exercises, daily ratings, etc) on the mHealth App Usability Questionnaire for Standalone mHealth Apps [63].

#### RAISE Effectiveness

Outcome analyses will focus on proximal caregiver-level outcomes, including mindful parenting, parenting stress, parenting self-efficacy, perceived barriers to youth treatment, and motivation for youth treatment. Secondary distal outcomes will include adolescent treatment initiation and retention. Linear regression will be used for continuous outcomes (ie, mindful parenting, parenting stress, perceived barriers to youth treatment, motivation for youth treatment), logistic regression for 3- and 6-month follow-up dichotomous outcomes (ie, treatment initiation and adherence to mandated treatment), and Poisson or negative binomial regressions for count outcomes (ie, number of treatment sessions attended). All analyses will include the intervention group as a predictor and control for baseline level of the outcome variable, application usage, and demographic characteristics (determined during preliminary analysis). Potential moderators and mediators of intervention effects will be explored using the PROCESS macro in SPSS, which uses a regression framework. Moderation analyses will involve computing interaction terms of intervention group (intervention vs comparison) by key demographic factors (eg, caregiver age, gender, race, mental health, substance use, and youth age, centered before computing interaction term for continuous variables). Mediational effects will examine the impact of intervention group on key proximal outcomes assessed at 3 months (ie, mindful parenting, parenting stress, parenting self-efficacy, perceived barriers to youth treatment, and motivation for youth treatment) and their impact on distal youth treatment engagement and retention outcomes assessed at 6 months. An “Intent to Treat” design, where all initially assigned to the intervention group are included in analyses, whether or not they used the intervention, will be used.

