**Methods:**

A randomized controlled trial with 60 caregivers of detained adolescents (ages 12-17 years) across the United States will be conducted. Caregivers will be recruited through passive and active techniques and randomized to receive RAISE (intervention) or an informational brochure (comparison). Self-assessment questionnaires will be completed at baseline and 3- and 6-month follow-up timepoints. The fully automated RAISE intervention includes an 8-week stress reduction intervention, self-monitoring and affirmational SMS text messaging, and resources related to navigating the juvenile legal system. Assessments include empirically validated measures of parenting stress, mindful parenting, parenting self-efficacy, adolescent services use, motivation for youth treatment, caregiver behavioral health, sociodemographics, and RAISE usability (intervention only). Caregivers will also participate in a semistructured qualitative exit interview at the 3-month (postintervention) timepoint. Descriptive statistics will examine recruitment, randomization, assessment, retention, and application usability. Independent samples *t* tests and chi-square analyses will determine whether randomization was successful based on multiple background variables; group differences will be accounted for in outcome analyses. Regression analyses will be used for outcome analyses, with an intent-to-treat design; analyses will include intervention group as a predictor and control for the baseline level of the outcome, application usage, and demographic characteristics. Potential moderators and mediators of intervention effects will be explored.

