### Intervention Condition (RAISE)

Caregivers (n=30) who are randomized to the RAISE intervention will receive access to the web application for a 6-month period. The first 3 months are considered the main intervention window, as this is the timeframe when the 8-week stress reduction intervention content is intended to be completed. Caregivers have the option to revisit this material at any time during the 6-month access period, and use of all RAISE app features is captured in app logs. Caregivers can access the web application on any device with an internet browser and log in using a unique username and password. RAISE is provided at no cost to participants.

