### Informational Brochure Condition (Comparison)

Caregivers (n=30) who are randomized to the comparison condition will receive an informational brochure about the juvenile legal system. Content for the brochure was adapted from existing guides distributed to caregivers by local jurisdictions in partnership with juvenile legal system professionals [54].

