##### Application Use Metrics

We will extract use metrics from the Chorus platform. Metrics will include the number of days of use, number of modules completed, time spent practicing mindfulness exercises, and responses to self-monitoring messages sent by the application.

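### Every effectiveness model adjusts for app usage, which arises after randomization and only in the RAISE arm, so the group coefficient is not the effect of being assigned to RAISE

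*Protocol article*

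**What the plan says.** The protocol article fixes the covariates in three places, and they agree.

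- RAISE Effectiveness: "All analyses will include the intervention group as a predictor and control for baseline level of the outcome variable, application usage, and demographic characteristics".
- RAISE User Engagement and Acceptability: the use metrics will be "included as control variables when examining intervention effectiveness".
- Abstract, Methods: the analyses "control for the baseline level of the outcome, application usage, and demographic characteristics".

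Usage comes from platform logs: "Metrics will include the number of days of use, number of modules completed, time spent practicing mindfulness exercises, and responses to self-monitoring messages" (Application Use Metrics). Caregivers "who are randomized to the RAISE intervention will receive access to the web application for a 6-month period" (Intervention Condition), whereas those "who are randomized to the comparison condition will receive an informational brochure about the juvenile legal system" (Informational Brochure Condition). Randomization directly follows the baseline assessment, so all usage comes after it.

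RAISE Effectiveness also declares an intent-to-treat design, "where all initially assigned to the intervention group are included in analyses, whether or not they used the intervention".

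No effectiveness model without usage is described. The rule in Quantitative Analysis to run models with and without certain variables covers only group differences in background and baseline variables.

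**The concern.** Usage is a consequence of assignment. It is plausibly the route by which RAISE works, and it has no natural value in the brochure arm. Adjusting for it removes from the group coefficient whatever benefit comes through use. It also brings in any prognostic difference between heavy and light users, which randomization does not balance.

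The article does not say how usage is coded for the 30 brochure caregivers. Neither obvious choice works:

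- **Coded 0:** usage is collinear with group, and the group coefficient refers to RAISE at zero use.
- **Coded missing:** a complete-case regression drops the whole brochure arm and the group effect cannot be estimated. Multiple imputation would have to invent app use for people never given the app.

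At stake are all the estimates of RAISE on caregiver and adolescent outcomes. Study Sample Size Determination says the effect size will be considered, cautiously, when the next trial is sized.

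**Working it through.** **Inputs from the protocol article.** N = 60, 30 per arm, α = .05, 4 predictors, f² = .15, stated power .62 (Study Sample Size Determination).

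**Assumed inputs, not in the article.** Usage is 0 in the brochure arm and scaled to mean 1 in RAISE, with a coefficient of variation (CV) between 0.3 and 1.5. The total effect is 0.5 SD where there is one. The baseline-outcome correlation is 0.6 (simulation A) or 0.5 (simulation B). Positive values below mean benefit.

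**1. The plan's own figure.** λ = f² × N = .15 × 60 = 9. The test of all 4 predictors on (4, 55) df has power 0.621, which reproduces .62. At the same f², a 1-df test of one coefficient has power 0.838; this is the reference for step 3. The stated figure is not in dispute here.

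**2. What the group coefficient estimates.** With usage 0 throughout the brochure arm, only RAISE caregivers inform the usage slope b. For a linear model, after baseline adjustment:

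group coefficient = D − b × m

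Here D is the effect of assignment and m = 1 is mean usage in RAISE. The coefficient equals D only if b = 0.

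| Situation | D | b × m | Group coefficient |
|---|---|---|---|
| Effect wholly proportional to use | 0.50 | 0.50 | 0.00 |
| Half through use | 0.50 | 0.25 | 0.25 |
| Effect unrelated to use | 0.50 | 0 | 0.50 |
| No effect; outcome 0.3 SD better per SD of usage, CV 0.5 | 0 | 0.3/0.5 = 0.60 | −0.60 |
| Same, CV 1.0 | 0 | 0.3/1.0 = 0.30 | −0.30 |

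**3. Loss of precision even when b = 0.** With 1:1 allocation, VIF = 1 + 1/(2 × CV²). Dividing f² = .15 by the VIF gives the power of the 1-df group test:

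| CV of usage | Correlation with group | VIF | Power (0.84 without usage) |
|---|---|---|---|
| 0.3 | .92 | 6.6 | 0.21 |
| 0.5 | .82 | 3.0 | 0.40 |
| 0.8 | .66 | 1.8 | 0.60 |
| 1.0 | .58 | 1.5 | 0.67 |
| 1.5 | .43 | 1.2 | 0.76 |

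**4. Simulation A.** 4,000 trials per scenario, gamma-distributed usage, CV 0.5 to 1.0, ANCOVA with and without usage.

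- Effect wholly through use: 0.50 SD and 57-63% power without usage; 0.00 SD and about 5% rejection with it.
- Constant 0.5 SD effect: unbiased, but power falls from about 65% to 27-46%.
- No effect, usage linked to prognosis as in step 2: coefficient −0.30 to −0.61 SD, 20-37% false positives. RAISE looks worse than the brochure.

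**5. Simulation B.** 4,000 trials per scenario, normal usage truncated at zero, CV 0.5 and 0.8, one extra baseline covariate. In the confounded cases an unmeasured trait drives both usage and outcome.

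- Wholly through use: about 0.00 SD with 5% rejection, against 56-58% without usage.
- Half through use: 0.24 to 0.25 SD with about 10% rejection, against 57-58%.
- No effect, confounded: −0.28 to −0.41 SD with 14-17% false positives. Without usage: about 0 and 5%.
- Wholly through use and confounded: the true benefit of about 0.5 SD is estimated as −0.28 to −0.42 SD, so the sign reverses.
- Usage unrelated to outcome: 0.50 SD recovered, but power falls from 59% to 23-33%.

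The two set-ups differ in usage distribution and confounding, and they agree on the direction of every error.

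**The case against.** Several points can fairly be made for the plan.

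- **Inclusion rule.** The article defines intent to treat as including everyone assigned. With usage coded 0 nobody is excluded, so the literal rule is kept. This stands. The conflict is with the effect of assignment regardless of use, which the rule exists to protect.
- **Coding.** A fuller analysis plan could say how usage is coded, and a model that lost the brochure arm would be noticed at once. True, but zero coding, the workable choice, is the one that gives the wrong estimand.
- **Total loss is the extreme case.** RAISE also sends weekly motivational text messages that no listed metric records, so part of any effect may bypass measured usage. This is plausible. The half-through-use case still loses half the effect.
- **Assumed values.** The CV, the prognosis link and the baseline correlation are not in the article, and the false-positive rate ranges from 14% to 37% across set-ups. The sizes are therefore illustrative.
- **Pilot status.** The article puts feasibility and acceptability first, calls the analyses underpowered and promises caution with effect sizes. Feasibility, usability and qualitative results are unaffected. But that caution concerns the unreliability of effect sizes from pilot studies; it does not remove a bias built into the model.

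**Conclusion.** The concern holds. As written, every effectiveness model conditions on a post-randomization variable that exists only in the RAISE arm, and its group coefficient does not estimate the effect of assignment. It would do so only if usage were unrelated to outcome. The article itself plans to examine that relation, and the relation would be expected if the app works by being used.

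Under an assumed total effect of 0.5 SD, the reported effect ranges from nil (wholly through use) through about half (half through use) to 0.50 SD with much reduced power (unrelated to use). With no effect and prognostic usage, RAISE appears harmful by roughly 0.3 to 0.6 SD. These sizes rest on the assumed usage distribution, correlations and confounding. The wrong estimand follows from the model itself. The flaw reaches all effectiveness estimates and should be corrected before the outcome data are analysed.

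**What to change.** Remove application usage from all intervention-effect, moderation and mediation models, and change the Abstract, RAISE User Engagement and Acceptability, and RAISE Effectiveness accordingly. Estimate the effect of RAISE with randomized group, the baseline value of the outcome and prespecified baseline covariates only.

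Keep usage as a separate exploratory question: association with outcome within the RAISE arm, adjusted for baseline and labelled non-randomized. A complier-average effect with randomization as the instrument is optional. It would need a stated definition of compliance and the assumption that assignment acts only through it. The text messages put that assumption in doubt, and with 30 per arm the estimate would be imprecise.

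The cost is a wording change before database lock. No new data are needed.

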### Parenting Stress

Among the potentially malleable factors contributing to adolescent treatment engagement is parenting stress (ie, stress reaction to demands of parenting), a well-documented impediment to treatment engagement, treatment progress, and a predictor of adverse youth outcomes such as substance misuse. Parent-child relationship (P-C-R) stress theory [12,13], one of the most widely tested and empirically supported parenting stress theories, posits that parenting stress arises from 3 domains: (1) parent (P); (2) child’s behavior (C); and (3) parent-child relationship (R). Each domain is associated with functional outcomes (eg, P with parent psychopathology [14,15], C with child behavior problems and psychopathology [16,17], R with parent-child relationship conflict [18,19]), which degrade the quality and effectiveness of parenting behavior and lead to increases in child emotional and behavioral problems. P-C-R theory proposes bidirectional effects (eg, child’s behavioral difficulty increases over time and parenting stress increases, resulting in further problems with parenting and child well-being; parent mental health leads to impaired parenting and increases child behavioral problems, which increases parenting stress). Caregivers’ reactions to the stress of parenting are key in propelling the process forward. For caregivers of legally involved adolescents, stress can be amplified by separation from their detained child and navigating the expectations imposed by the carceral system.

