##### Adolescent Services Use

The Child and Adolescent Services Assessment [61] obtains information about service use for mental health and substance use needs across multiple sectors (eg, schools and the legal system), including details about the type of treatment facility, professional discipline of provider(s), outpatient services, and out-of-home placements. We adapted this instrument to also assess whether services were mandated by the legal system. Outcomes of focus will include whether the adolescent completed any behavioral health services following release into the community (yes or no) and whether they complied with mandated services (yes or no). Barriers to adolescent services are also assessed (16 barriers; language, transportation, cost, stigma, etc). The assessment focuses on the 3 months before the adolescent’s detention (at baseline) and for follow-ups in the 3 months since the last assessment.

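### The exploratory mediation relates 3-month caregiver measures to 6-month youth treatment and leaves out treatment already begun in months 0-3, so the mediator-to-outcome path may be biased

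*Protocol article*

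**What the plan says.** All references are to the Methods of the protocol article unless noted.

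- **Mediators** (RAISE Effectiveness): "Mediational effects will examine the impact of intervention group on key proximal outcomes assessed at 3 months". Five are listed: mindful parenting, parenting stress, parenting self-efficacy, perceived barriers and motivation for treatment.
- **Outcome of the mediation** (same section): "their impact on distal youth treatment engagement and retention outcomes assessed at 6 months".
- **Covariates** (same section): every analysis includes the intervention group and will "control for baseline level of the outcome variable, application usage, and demographic characteristics (determined during preliminary analysis").
- **Service windows** (Adolescent Services Use): the baseline assessment covers the 3 months before detention. The instrument is then used "for follow-ups in the 3 months since the last assessment", so months 0-3 and months 3-6 are recorded separately.
- **Service outcome** (same section): whether the adolescent "completed any behavioral health services following release into the community (yes or no").
- **Treatment initiation is also a 3-month outcome** (RAISE Effectiveness): "logistic regression for 3- and 6-month follow-up dichotomous outcomes (ie, treatment initiation and adherence to mandated treatment").
- **Theory** (Introduction, Parenting Stress): "P-C-R theory proposes bidirectional effects".
- **Status**: mediators are to be explored, and Study Sample Size Determination calls the analyses of this pilot underpowered.

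**The concern.** Randomisation protects the path from arm to mediator. It does not protect the path from mediator to outcome, which relies on covariates. Treatment begun in months 0-3 comes before or alongside the 3-month mediator and probably predicts treatment in months 3-6. If it also moves caregiver stress, perceived barriers or motivation, it is a common cause of mediator and outcome. The stated baseline term cannot stand in for it, because that term describes services before detention.

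There are two related gaps. First, in the mediator-to-outcome model the outcome is treatment, so controlling for the outcome's baseline does not bring in the baseline value of the mediator. Second, the yes/no service outcome can be read as cumulative since release. On that reading, part of the 6-month outcome happened before the mediator was measured.

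What is at stake is the mechanism in the hypothesised model (Figure 1). The Conclusions say the findings will inform a larger trial, and this bias would not shrink as the sample grows.

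**Working it through.** **1. The plan's own figure.** The only quantitative statement is power of .62 for N = 60, α = .05, 4 predictors and f² = .15. A noncentral F test with 4 and 55 df and λ = 0.15 × 60 = 9 gives 0.6208, so the figure reproduces. It concerns the primary regression. No figure is given for the mediation.

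**2. Timeline.**

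| Window | Measured | Role in the stated mediation model |
|---|---|---|
| 3 months before detention | services | baseline covariate |
| Months 0-3 | services | not used |
| Month 3 | five caregiver measures | mediators |
| Months 3-6 | services | outcome, or part of it if cumulative |

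**3. Assumed inputs (none is in the documents).** Early treatment by month 3: p = 0.40. It lowers 3-month stress by d = 0.3 to 0.8, with stress SD about 1 and residual variance 0.75 given baseline stress. Treatment in months 3-6 without early treatment: 30%. Odds ratio for continuing: 3 to 10. True effect of stress on later treatment: zero. Baseline stress and baseline services are in the model and application usage is left out, so the result isolates month 0-3 treatment.

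**4. Approximate bias of the path (omitted-variable formula).**

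bias ≈ ln(OR) × [−d·p(1−p)] / [0.75 + d²·p(1−p)], with p(1−p) = 0.40 × 0.60 = 0.24

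- d = 0.3, OR 3: 1.099 × (−0.072/0.772) = −0.10
- d = 0.5, OR 6: 1.792 × (−0.120/0.810) = −0.27
- d = 0.8, OR 10: 2.303 × (−0.192/0.904) = −0.49

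Simulation gives −0.10 to −0.48 log-odds per unit of stress, in agreement. With d = 0 the bias is zero. If early treatment raises stress, d changes sign and so does the bias.

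**5. False-positive rate of the stress-to-treatment path, N = 60.**

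| Setting | Month 0-3 treatment omitted | Included, months 3-6 outcome |
|---|---|---|
| d = 0.5, OR 6, months 3-6 outcome | 11.6% | 5.1% |
| d = 0.5, OR 6, cumulative outcome | 30.0% | as above |
| full range, months 3-6 outcome | 6-32% | about 4-6% |
| full range, cumulative outcome | 14-58% | as above |

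A further simulation of the same path gave 11-35% without month 0-3 treatment and about 6% with it. The cumulative outcome does worse because it contains the early treatment itself: 0.40 + 0.60 × 0.30 = 0.58 would be recorded as yes, and 0.40/0.58 = 69% of those were settled by month 3. Nor can month 0-3 treatment be used as a covariate for that outcome, since everyone treated early is a yes.

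**6. Indirect effect.** Here the arm raises early treatment (25% v 55%), OR is 6 and the true stress effect is zero. Median spurious indirect effect (log-odds) at N = 60:

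| d | Months 3-6 | Cumulative | Both paths significant, omitted (months 3-6 / cumulative) |
|---|---|---|---|
| 0.3 | 0.005 | 0.012 | 0.8% / 0.6% |
| 0.5 | 0.021 | 0.039 | 1.7% / 2.7% |
| 0.8 | 0.055 | 0.119 | 3.1% / 6.6% |

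With adjustment (months 3-6 outcome) the median is about 0. At N = 600, months 3-6 outcome, both paths are significant in 7%, 39% and 84% for the three values of d, against 2-5% adjusted.

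**7. Baseline mediator values.** In a simulation where baseline stress confounded the path, adding it reduced false positives from 13% to 5%. The strength of that confounding was assumed.

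**8. Cost of adjusting.** Suppose stress truly acts before month 3 (assumed effects −0.8 log-odds per unit on early treatment, −0.4 on later treatment, continuation OR 6). Detection of the stress path at N = 60 then falls from 43-44% to 17% with adjustment. It falls to 9-11% in adolescents not yet in treatment at 3 months, about 34 of the 60.

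**The case against.** **Exploratory status.** The mediation is exploratory in a pilot focused on feasibility, and youth treatment is a secondary, distal outcome. This stands and limits the weight of the point. It does not answer it: the exploratory label covers chance and low power, while confounding persists in any sample size.

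**Unknown size and direction.** No passage gives the share treated by month 3 or the effect of treatment on stress. Adolescents are detained at enrolment and release timing is not stated, so little post-release treatment may precede the mediator. A reader might infer from the bidirectional theory that starting treatment lowers stress. The theory section links stress with child behaviour and parent mental health and does not say that. The Background says caregivers must mobilise substantial resources to engage treatment, so early treatment could raise stress instead. This stands: the bias could create an apparent mechanism or hide a real one.

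**The adjustment can remove the mechanism.** The 8-week programme lies within months 0-3, and initiation is itself a 3-month outcome. Lower stress may work by getting treatment started early, and conditioning on month 0-3 treatment blocks that route. This stands, and it rules out presenting the adjusted model as simply the correct one. Restricting to adolescents not yet treated also selects on a post-randomisation variable.

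**Conclusion.** The point holds for the mediator-to-outcome path. The article states its covariate list, and that list leaves out a measured variable that may confound all five mediators. Under the assumed inputs the stress path is biased by about 0.10 to 0.48 log-odds per unit, and its false-positive rate at N = 60 is 6-32% in place of about 5%. It is higher if the outcome is cumulative. If early treatment does not change the mediators, this bias is absent.

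A reader might conclude that a false indirect effect would regularly be declared. At N = 60 the figures do not support that: both paths are significant in about 1-7% of simulated trials. The harm is mainly a biased path and a biased indirect-effect estimate, which could mislead planning of the next trial. Nor does the point touch the comparison between arms. It is a modest, inexpensive improvement to an exploratory analysis.

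**What to change.** In the mediator-to-outcome models:

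1. Add the baseline value of each mediator, which is already collected.
2. Define the 6-month service outcomes as services in months 3-6, so that the mediator precedes the outcome.
3. Report the path with and without month 0-3 treatment status as a covariate.
4. Describe the result as associational, and say that the adjusted version concerns later treatment given earlier treatment.

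The cost is one extra model per mediator and outcome, and wider intervals. The adjusted version also drops any effect of stress that runs through treatment started before month 3, so it should stand beside the unadjusted version and not replace it. An analysis restricted to adolescents not yet in treatment at 3 months should be omitted or shown descriptively only. Whether application usage belongs in these models is a separate question.
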